#### Sample size considerations

The study sample size is *n* = 1200, with equal size strata (*n* = 150) by language, health literacy level, and information delivery mode (Fig. 4). This sample size is based on a 2x2x2 full factorial design and will satisfy the requirements for analysis of the two primary aims and the four alternative hypotheses paired with each aim. The minimum sample size is calculated for a power of 0.80 and a two-sided *α = 0.05* level of significance (Table 3). In general, a larger sample size is needed for greater variation of scores within study arms and strata, lower within-person correlations of scores, and higher loss-to-follow-up. To maximize power, we chose conservative values based upon our prior studies. We increased the sample size by 20% to account for the heterogeneity in patients among the four study sites, and by a conservative additional 25% to account for possible attrition. Based upon other 12-month ED intervention follow-up studies [10], HIV/STD testing studies [57–59], and studies conducted at our own ED [60, 61], a 25% attrition rate at 12 months likely is a worst-case scenario. We expect that our experience and enhanced measures to encourage and facilitate follow-up will result in higher follow-up rates. As of publication of this manuscript, 1165 participants enrolled completed the three-month follow-up.

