**Fig. 4 Fig4:**

Sample size by study arm, language, and health literacy level

**Table 3 Tab3:** Sample size rationale by primary aims

Primary Aims	Minimum sample by stratum	Total minimum sample	Rationale and assumptions for minimum sample sizes and final sample sizes for each primary aim
Aim 1. Short-term improvement in HIV/AIDS and HIV testing knowledge ** HA1**: 3-way interaction (mode*language*literacy level) ** HA2**: 2-way interaction (mode*language or literacy level) ** HA3**: no interaction (difference by mode only) ** HA4**: no difference	**125** This **minimum** sample size by stratum will yield a power of 0.80, 0.97 and 0.99 for testing HA1, HA2, HA3 versus HA4 (HA4 as the NULL) Final sample per stratum (information delivery mode, language, and health literacy level) is 150	**1000** The **final sample** after adding 20% to account for the heterogeneity in patients among study sites is **1200** = 1000*(1 + 20%)	• Based on our prior video studies [17, 19, 21], we assume that the scores on the 25-item questionnaire is a normal distribution with a standard deviation of ~ 3 • Before information delivery, mean scores of the two arms are assumed to be the same (due to random assignment) per stratum • Short-term within-person correlation is 0.7 or higher [21] • The pictorial brochure will improve knowledge by an average of 2 points. The video will improve the knowledge by an average of 3.5 points. The effect size is Δ = 3.5–2 = 1.5. (HA3) • 2-way intrxn (mode*language or literacy level) effect size is Δ = 1.5 + 0.75 = 2.25. (HA2), e.g. for those speaking English OR with high health literacy • 3-way intrxn (mode*language*literacy level) effect size is Δ = 1.5 + 0.75 + 0.75 = 3.0, e.g. for those speaking English AND having high literacy AND watching the video

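### Table 3 (Aim 1) enters subgroup mode effects as interaction effect sizes; the implied two-way contrast is 0.75, with power 0.72 to 0.79 rather than 0.97, and the three-way contrast is not fixed

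*Protocol article*

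**What the plan says.** All of this is in the protocol article.

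- *Sample size considerations*: "This sample size is based on a 2x2x2 full factorial design", and "The minimum sample size is calculated for a power of 0.80 and a two-sided *α = 0.05* level of significance".
- *Table 3, Aim 1*, assumptions: "we assume that the scores on the 25-item questionnaire is a normal distribution with a standard deviation of ~ 3"; "Short-term within-person correlation is 0.7 or higher". The brochure is assumed to add 2 points and the video 3.5, a mode effect of 1.5 (HA3).
- *Table 3, Aim 1*, interactions: "2-way intrxn (mode*language or literacy level) effect size is Δ = 1.5 + 0.75 = 2.25", illustrated by patients who speak English or have high health literacy. Then "3-way intrxn (mode*language*literacy level) effect size is Δ = 1.5 + 0.75 + 0.75 = 3.0", illustrated by patients with both features who watch the video.
- *Table 3, Aim 1*, result: at a minimum of 125 per stratum, the "sample size by stratum will yield a power of 0.80, 0.97 and 0.99 for testing HA1, HA2, HA3 versus HA4". The same row adds: "Final sample per stratum (information delivery mode, language, and health literacy level) is 150".
- *Primary aims analysis*: the parameters of interest are the study-arm coefficient and its interactions with language and health literacy.

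**The concern.** An interaction measures how much the mode effect changes between groups. The 2.25 and 3.0 in Table 3 are the whole mode effect in a favoured group, with the common 1.5 points included. The sample size is therefore argued on one quantity while the analysis tests another, smaller one.

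This matters because the trial is meant to tell emergency departments whether to choose video or brochure by language or literacy. A reader who trusts 0.97 would take a non-significant two-way interaction as good evidence that tailoring is not needed. The design does not give that assurance for the increment that Table 3 itself assumes.

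**Working it through.** **Inputs** (Table 3, Aim 1, and *Sample size considerations*): SD 3; pre-post correlation r = 0.7 (the stated lower limit); two-sided α = 0.05; n = 125 per cell (minimum) or 150 (final); eight equal cells.

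**Formulas** (normal approximation):
- Change-score SD: s = 3√(2(1 − 0.7)) = 2.324. ANCOVA residual SD: s = 3√(1 − 0.7²) = 2.142.
- SE of the three-way contrast (eight cell means): s√(8/n).
- SE of a two-way contrast pooled over the third factor: s√(4/(2n)).
- SE of the overall mode effect: s√(2/(4n)).
- Power ≈ Φ(|Δ|/SE − 1.96), plus the opposite tail, which matters only when Δ is near 0.

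At n = 125 the SEs are 0.588, 0.294 and 0.147 (change score), or 0.542, 0.271 and 0.135 (ANCOVA).

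**Step 1. Try to reproduce the stated figures.** Enter 3.0, 2.25 and 1.5 as the three contrasts, by change score:
- 3.0/0.588 = 5.10, power 0.999
- 2.25/0.294 = 7.65, power above 0.999
- 1.5/0.147 = 10.2, power above 0.999

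ANCOVA gives higher power still. So the printed effect sizes and correlation do not return 0.80 and 0.97. Two other routes come close, and each departs from the table:
- Change scores with r = 0 (SD 4.243) and contrasts 3.0 / 2.25 / 1.5 give 0.798 / 0.987 / above 0.999. This drops the stated correlation.
- ANCOVA at r = 0.7 with a contrast of 1.5 over eight, four and two cells of 125 gives 0.790 / 0.975 / above 0.999. This uses neither 2.25 nor 3.0 as the contrast.

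**Step 2. Two-way contrast.** 2.25 − 1.5 = 0.75.

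| n per cell | Change score | ANCOVA |
|---|---|---|
| 125 | 0.75/0.294 = 2.55, power 0.72 | 0.75/0.271 = 2.77, power 0.79 |
| 150 | 0.75/0.268 = 2.80, power 0.80 | 0.75/0.247 = 3.03, power 0.86 |

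Power of 0.97 for a contrast of 0.75 would need about 284 (change score) or 241 (ANCOVA) per cell. At 125 per cell it would need a correlation of about 0.87 by change score.

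**Step 3. Three-way contrast.** This needs the mode effect in all four language-by-literacy strata, which Table 3 does not list. Two patterns fit its words:
- *Increments add* (1.5, 2.25, 2.25, 3.0): 3.0 − 2.25 − 2.25 + 1.5 = 0. Power equals α, 0.05.
- *Only English/higher literacy differs* (1.5, 1.5, 1.5, 3.0): 3.0 − 1.5 − 1.5 + 1.5 = 1.5. Power is 0.72 or 0.79 at 125 per cell, and 0.80 or 0.86 at 150.

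The pooled two-way contrast is 0.75 under both patterns. In the second, the English average is (1.5 + 3.0)/2 = 2.25, against 1.5 for Spanish. Step 2 therefore does not depend on which pattern was meant.

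**Step 4. Contrasts detectable with 80% power by ANCOVA** ((1.96 + 0.84) × SE):

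| n per cell | Mode | Two-way | Three-way |
|---|---|---|---|
| 125 | 0.38 | 0.76 | 1.52 |
| 150 | 0.35 | 0.69 | 1.39 |

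**The case against.** Four arguments can be made for the table.

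1. **HA1 and HA2 are separate alternatives, and the figures are examples.** A reader might infer that Table 3 implies a three-way interaction of exactly zero, and hence that 0.80 is simply wrong. The text does not force that. If only one stratum differs under HA1, the contrast is 1.5 and ANCOVA power is 0.79, close to 0.80. This stands.

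2. **Some route does give 0.80 / 0.97 / 0.99.** ANCOVA is a named method, and a contrast of 1.5 throughout nearly matches all three figures. So it would be wrong to say that the figures can arise only by ignoring the correlation, or that no calculation yields them. For the two-way test, however, this route needs a contrast of 1.5, for example 2.25 against 0.75 around an average of 1.5. Table 3 does not state such a coding; it adds 0.75 to 1.5.

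3. **Power is stated against HA4, no difference at all.** On that reading the test is not of the interaction alone. Power would then be near 1: a mode effect of 1.5 in a single stratum of 125 per arm already has power above 0.99. The printed figures are not explained this way either, and the analysis section makes the interaction coefficients the target.

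4. **The trial has 150 per cell.** At that size the two-way contrast of 0.75 reaches 0.80 to 0.86, which meets the protocol's 0.80 target. This stands and softens the consequence. A reader might infer that the trial is underpowered for HA2; the documents do not support that at the final size, although the protocol assigns the extra 20% to heterogeneity among sites.

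**Conclusion.** The point holds as a misstatement of effect sizes and power, not as proof of an inadequate sample.

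- **Firm:** 2.25 and 3.0 are subgroup mode effects, and together with r = 0.7 they do not produce the printed powers. The implied two-way contrast of 0.75 has power 0.72 to 0.79 at 125 per cell, against 0.97 stated.
- **Conditional:** the stated 0.80 for HA1 is about right if the three-way contrast is 1.5, and has no basis if the increments are additive. The table leaves this open.

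The numbers rest on SD 3, r = 0.7, equal cells, independent patients and the two-way test pooled over the third factor. A higher correlation, which the plan allows, would raise every power.

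**What to change.** In Table 3, Aim 1:

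1. List the assumed mode effect in each of the four language-by-literacy strata under HA1 and under HA2, and show the interaction contrasts that follow.
2. Replace 0.80 and 0.97 with the power for those contrasts, naming the analysis (change score or ANCOVA) and the n per cell. Alternatively, give the contrasts detectable with 80% power by ANCOVA: 0.38 (mode), 0.76 (two-way) and 1.52 (three-way) at 125 per cell; 0.35, 0.69 and 1.39 at 150.
3. State that a three-way contrast smaller than about 1.4 to 1.5 points is not powered, and that a non-significant interaction test is not evidence that tailoring is unnecessary. Report interaction estimates with confidence intervals so that readers can see what has been excluded.

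The cost is a rewritten table row and a sentence or two of text. Sample size, randomisation and data collection do not change.

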Aim 2. Retention of HIV/AIDS and HIV testing knowledge at 3, 6, 9, and 12 months ** HA1**: 3-way interaction (mode*language*literacy level) ** HA2**: 2-way interaction (mode*language or literacy level) **HA3**: no interaction (difference by mode only) ** HA4**: no difference	**100** This **minimum** sample size by stratum will yield a power of 0.80, 0.97 and 0.99 for testing HA1, HA2, and HA3, versus HA4 (as the NULL)	**800** After adding 25% to account for loss-to-follow-up and 20% for heterogeneity among study sites, the **final sample** size is **1200** = 800*(1 + 25%)*(1 + 20%)	• Long-term within-person correlation is 0.4 or higher • The scores on the knowledge questionnaire in the pictorial brochure arm will degrade to the pre-information baseline level with an average drop of 2 points by 12 months. The score in the video information arm will degrade by an average drop of 1 point. So, compared to baseline, the difference (effect size) in long-term retention of information in the video arm as compared to the pictorial brochure arm is Δ = (3.5–1)-(2–2) = 2.5. • We will assume a similar effect size for 2- and 3-way interactions

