#### Secondary aims and exploratory aim analyses

Our main secondary aim is assessing HIV re-testing behavior (Table 5). For our sample size (*n = 150/stratum*), we will have adequate power to detect a ≥ 15% absolute difference (Δ) in HIV testing behaviors (re-testing at 12 months, HIV testing outside of the study) by group within strata (information delivery mode, language and health literacy level) (assumes ≥75% follow-up, β = 0.2, α = 0.05). A ≥ 15%Δ is reasonable, per other HIV testing research [16, 66, 67]. Per the IMB model, we also will investigate differential changes in short-term (in ED) motivation and behavioral skills by information delivery mode, language, and health literacy level. Further, we will (1) assess if increase and retention of knowledge, motivation, and behavioral skills impacts behaviors (HIV testing); (2) examine the interrelationships of model components (e.g., path coefficients [34]); and (3) assess the moderating influence of information delivery mode, health literacy level and language on motivation, behavioral skills and behavior change. Mediation/moderation models using structural equation modeling and other recommended approaches will be used [68–73]. We also will examine other factors potentially associated with HIV re-testing, such as demographic characteristics, study site, and changes in HIV risk-taking behavior over time.

**Table 5 Tab5:** Analyses of secondary and exploratory aims

***Secondary aims***	***Measurements***	***Analytic methods***
**Motivation** (1) attitudes toward need for HIV testing for oneself, (2) beliefs regarding the value of HIV testing, and (3) self-perceived risk for having an HIV infection	HIV testing motivation and behavioral skills questionnaire; post- vs. pre-information delivery	• Paired t-tests or signed rank tests • Generalized linear mixed-effects regression
**Behavioral skills** (1) initiating or seeking of HIV testing, (2) interpretation and response to HIV test results, and (3) assessment of HIV risk and need for repeat testing	HIV testing motivation and behavioral skills questionnaire; post- vs. pre-information delivery	• Paired t-tests or signed rank tests • Generalized linear mixed-effects regression

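### Power for re-testing within strata is claimed with no base rate and fails over most rates at the stated follow-up; separately, the Aim 2 inflation covers 20% loss, not 25%

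*Protocol article*

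**What the plan says.** **Re-testing.** Under *Secondary aims and exploratory aim analyses*, re-testing is named as the main secondary aim. For 150 per stratum the article says "we will have adequate power to detect a ≥ 15% absolute difference" in testing behaviours between groups inside strata, assuming at least 75% follow-up, β = 0.2 and α = 0.05. No re-testing rate is given for either arm. The baseline-comparison section sets two-tailed 0.05 for all analyses. *Sample size considerations* defines the 150: "The study sample size is *n* = 1200, with equal size strata (*n* = 150) by language, health literacy level, and information delivery mode". It is therefore the size of one language-by-literacy-by-mode cell.

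**Aim 2.** Table 3 sets a minimum of 100 per cell (800 in total) and states: "This minimum sample size by stratum will yield a power of 0.80, 0.97 and 0.99 for testing HA1, HA2, and HA3, versus HA4". The total becomes 1200 "After adding 25% to account for loss-to-follow-up and 20% for heterogeneity among study sites", computed as 800 × 1.25 × 1.20. *Sample size considerations* treats the 25% as a proportion lost: "a 25% attrition rate at 12 months likely is a worst-case scenario". *Follow-up assessments* adds that anyone who misses the 3-month follow-up is discontinued and that the recruitment quota is adjusted to replace them.

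**The concern.** Power to detect a fixed absolute difference between two proportions depends strongly on where the proportions lie. A power claim without a base rate is safe only if it holds at the least favourable rate, and this one does not. The trial is meant to tell emergency departments whether to choose the delivery mode by language and health literacy. A non-significant re-testing result inside one stratum could be taken as evidence that the modes perform alike, on the strength of power that the design may not have.

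The Aim 2 matter is the familiar confusion of two inflation rules. To end with n after losing a fraction d, one enrols n/(1 − d), not n × (1 + d). At d = 25% the two differ enough that the stated worst case is not fully covered.

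**Working it through.** **Re-testing**

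Inputs from the article: 150 per cell, 75% follow-up, difference 0.15, two-sided α = 0.05, target power 0.80, 1:1 allocation. The lower rate p₁ is not given, so it is assumed and varied.

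- Completers per arm in one language-by-literacy stratum: 150 × 0.75 = 112.5, taken as 112.
- With p₂ = p₁ + 0.15 and p̄ the mean of the two rates, power = Φ{[0.15√n − 1.96√(2p̄(1 − p̄))] / √(p₁(1 − p₁) + p₂(1 − p₂))}.
- Least favourable case, 42.5% vs 57.5%, n = 112: (1.587 − 1.386)/0.699 = 0.288, so power = Φ(0.288) = 0.61.

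| Lower vs higher rate | Power, 112 per arm | Power, 150 per arm (no loss) |
|---|---|---|
| 10% vs 25% | 0.845 | 0.93 |
| 15% vs 30% | 0.77 | 0.88 |
| 20% vs 35% | 0.71 | 0.83 |
| 30% vs 45% | 0.64 | 0.77 |
| 42.5% vs 57.5% | 0.61 | 0.74 |
| 50% vs 65% | 0.62 | 0.75 |
| 60% vs 75% | 0.67 | 0.795 |
| 70% vs 85% | 0.77 | 0.88 |
| 75% vs 90% | 0.845 | 0.93 |

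At 112 per arm, power reaches 0.80 only if the lower rate is at most about 13% or at least about 72%. For 80% power at every base rate, 174 completers per arm are needed, or 174/0.75 = 232 enrolled per cell.

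Largest difference needed for 80% power (rates centred on 50%), at 75% follow-up:

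- One stratum, 112 per arm: 18.6 points.
- One language or one literacy level, 300 × 0.75 = 225 per arm: 13.2 points.
- All participants, 600 × 0.75 = 450 per arm: 9.3 points.

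**Aim 2**

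- Plan's figure: 800 × 1.25 × 1.20 = 1200. It reproduces exactly.
- Loss covered by a factor of 1.25: 1 − 1/1.25 = 20%.
- Correct inflation at 25% loss: 800 × 1.20/0.75 = 1280, or 160 per cell, 80 patients more than 1200.
- Completers from 1200 at 25% loss: 1200 × 0.75 = 900, or 112.5 per cell. The plan's logic needs 100 × 1.20 = 120.
- Effective size after the heterogeneity allowance: 112.5/1.20 = 93.75, about 94 per cell.
- Power for HA1, taking the plan's 0.80 at 100 per cell as given: the standardised effect is 1.960 + 0.842 = 2.802. At 93.75 it is 2.802 × √0.9375 = 2.713, so power = Φ(2.713 − 1.960) = 0.77. On the same basis 0.97 becomes 0.96 for HA2, and 0.99 stays at about 0.99 (0.986) for HA3.

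**The case against.** **Re-testing.** The sentence is loosely worded: its bracket lists delivery mode alongside language and literacy, so a single-stratum comparison of video with brochure is not the only reading. If two strata are pooled (225 per arm), minimum power for 15 points is 0.89; with everyone (450 per arm) it is 0.995. This stands as a qualification, but tying the claim to 150 per stratum favours the single-stratum reading. It is also fair that base rates outside 13% to 72% are possible: participants agreed to a test at enrolment and are later offered a free home kit. An article may leave the base rate to a fuller document. What it cannot do is state the power unconditionally when it holds only for some rates. A reader might take 0.61 as the power of the comparison. The documents do not support that; it is the minimum over rates that the article does not give.

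**Aim 2.** The defence is stronger here. A reader might infer that 1200 leaves only 94 people per cell, fewer than the minimum of 100. It does not: 112.5 remain, and 94 is an effective size after setting aside the 20% site allowance. A reader might also compute HA1 power from a change score (SD 3, correlation 0.4, difference 2.5), obtain 0.74, and report a fall from 0.80. That model gives only 0.767 at 100 per cell, so the slip itself costs about 0.03 on either basis. Replacement of 3-month non-completers also helps: the article reports 1165 enrolled participants past month 3, and if no more than 20% of the 1200 are lost after that point, the effective 100 per cell is kept. The printed calculation takes no credit for this.

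Finally, one might ask that the pooled comparison be made the main re-testing analysis. That is a preference, not a correction; Table 5 already lists a Cochran-Mantel-Haenszel test.

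**Conclusion.** The main point holds. On the reading that 150 per stratum supports, with 75% follow-up and two-sided 0.05, power for a 15-point difference is 0.61 to 0.80 for lower rates of about 13% to 72%, and reaches 0.80 only at or beyond those limits. Attrition is not the whole cause, since the minimum with no loss is 0.74. The conclusion depends on that reading and on the unstated base rate; it does not carry over to comparisons pooled over two or four strata.

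The Aim 2 point holds as a minor one. The 1200 covers 20% loss, and the plan's own inputs at 25% give 1280. The consequence is an effective 94 per cell and HA1 power of about 0.77 in place of 0.80, if the plan's 0.80 at 100 per cell is accepted and no credit is taken for replacement. It does not show that Aim 2 is inadequately powered.

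**What to change.** - **Re-testing:** either state the base rate for which 80% power for 15 points holds within a stratum, or replace the claim with detectable differences at 80% power and 75% follow-up: up to about 19 points within one language-by-literacy stratum, 13 points within one language or one literacy level, and 9 points overall. Say which comparison the figure refers to.
- **Aim 2:** state that 1200 allows for 20% loss at 12 months, or keep 25% and report power at an effective 94 per cell. If replacement of 3-month non-completers is relied on, say so and apply the loss allowance to the period after month 3.

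The cost is a few restated figures. No extra patients and no change to the analysis are needed.

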#### Primary aims analysis

For Aim 1, we expect that HIV/AIDS and HIV testing knowledge scores can be reasonably approximated by a normal distribution (Table 4). We will compare differences in pre- vs. post- changes in scores between information delivery modes by paired t-tests. If the data are not normally distributed, we will use signed-rank tests. All tests will be executed on an intention-to-treat basis (non-adherence to assigned information delivery mode likely is minimal). Comparisons will first be made for each stratum. MANOVA/ANCOVA will be used for combined samples where language and literacy level are used as stratifying (main) factors. To further account for baseline covariates (e.g., demographic characteristics), a generalized linear mixed-effect model will be fit to the data. The parameters of interest are the coefficients of the dummy variable indicator of study arm assignment and its interactions with language and health literacy level.

**Table 4 Tab4:** Analyses of primary aims

Primary aims	Measurements	Analytic methods
Aim 1. Short-term improvement in HIV/AIDS and HIV testing knowledge **HA1**: 3-way interaction (mode*language*literacy level) **HA2**: 2-way interaction (mode*language or literacy level) **HA3**: no interaction (difference by mode only) **HA4**: no difference	HIV/AIDS and HIV testing knowledge questionnaire at baseline in ED at time of HIV testing, post- vs. pre-information delivery	• Paired t-tests • Signed-rank tests • MANOVA/ANCOVA • Generalized linear mixed-effects regression
Aim 2. Retention of HIV/AIDS and HIV testing knowledge at 3, 6, 9, and 12 months **HA1**: 3-way interaction (mode*language*literacy level) **HA2**: 2-way interaction (mode*language or literacy level) **HA3**: no interaction (difference by mode only) **HA4**: no difference	HIV/AIDS and HIV testing knowledge questionnaire at 3, 6, 9, and 12 months vs. baseline (post-information delivery)	• Paired t-test for each follow-up vs. baseline • Linear mixed-effects regression (assuming constant degradation over time) • Broken-stick linear mixed-effects regression (for non-constant degradation over time)

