If a linear assumption is supported by data, the linear predictor in the above model will be expressed as *α*_*0*_ *+ β*_*1*_*[time] + β*_*2*_*[time]*R*_*i*_*[mode]*, where *β*_*1*_ and *β*_*2*_ capture HIV/AIDS and HIV testing knowledge retention rate over time and the difference in the rate between two delivery modes. We will further evaluate the 2- and 3-way interactions *β*_*2*_*[time]*[language]*R*_*i*_
*[mode]* and *β*_*2*_*[time]*[health literacy level]*R*_*i*_*[mode]* and possibly (if data allow) 4-way interactions *β*_*2*_*[time]*[language]*[health literacy level]*R*_*i*_*[mode]*, to investigate the interaction of information delivery mode with language and health literacy and whether one delivery model works better in certain sub-groups. Our analysis by time will permit us to determine if and when HIV/AIDS and HIV testing knowledge degrades, and if and when knowledge reaches baseline pre-information levels (i.e., before an intervention), which would suggest a need for repeat delivery of this information at subsequent HIV testing encounters within 12 months. We also will determine if degradation varies by information delivery mode, language, and health literacy level. We recognized that there is no established minimum standard for what level of HIV/AIDS and HIV testing knowledge is necessary or desired; however, we believe that it should be at least greater than pre-information knowledge levels, and will plan the analyses accordingly.

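### Aim 2 is powered on a 2.5-point gain over the pre-information score but analysed as decline from the post-information score, where the plan's own figures give 1.0 point

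*Protocol article*

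**What the plan says.** The Sample size considerations section sets the design: "The study sample size is *n* = 1200, with equal size strata (*n* = 150) by language, health literacy level, and information delivery mode". On the error rates it says "The minimum sample size is calculated for a power of 0.80 and a two-sided" test at α = 0.05.

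Table 3 gives the assumptions. On the score, it assumes "the scores on the 25-item questionnaire is a normal distribution with a standard deviation of ~ 3". In the Aim 2 row, "Long-term within-person correlation is 0.4 or higher". The brochure arm gains 2 points and loses all 2 by 12 months. The video arm gains 3.5 and loses 1. The Aim 2 effect is then taken against the pre-information level: "retention of information in the video arm as compared to the pictorial brochure arm is Δ = (3.5–1)-(2–2) = 2.5". The interactions are assumed to be of similar size. At the minimum of 100 per cell, this "sample size by stratum will yield a power of 0.80, 0.97 and 0.99 for testing HA1, HA2, and HA3, versus HA4 (as the NULL").

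Table 4, under Primary aims analysis, defines the Aim 2 measurement as "HIV/AIDS and HIV testing knowledge questionnaire at 3, 6, 9, and 12 months vs. baseline (post-information delivery"). The text of that section repeats the post-information reference for the paired t-tests. It names the time coefficients and their interactions with mode as the parameters of interest, and it describes β2 as the difference between modes in the rate of retention. The same section also says what level of knowledge would count: "we believe that it should be at least greater than pre-information knowledge levels, and will plan the analyses accordingly".

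**The concern.** The word baseline means the pre-information score in Table 3's Aim 2 effect and the post-information score in Table 4. The two references do not give the same effect. Of the 2.5 points, 3.5 − 2 = 1.5 are the short-term difference already tested in Aim 1. Only 2 − 1 = 1.0 is a difference in what is lost afterwards, and loss is what the stated comparisons and the slope measure.

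The interaction hypotheses HA1 and HA2 decide whether information should be tailored by language and health literacy, and HA4 (no difference) is to be read as either mode being suitable for everyone. If power for the interactions is well below the stated value, a missed interaction could be reported as evidence that tailoring is unnecessary.

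The post-information score is also itself affected by the randomised mode, so decline from it and knowledge held at 12 months are different questions. A purely hypothetical case shows this. If video went from +3.5 to +0.5 and brochure from +2.0 to +0.5, knowledge at 12 months would be equal, yet decline would favour the brochure by 1.5 points.

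**Working it through.** **Inputs.** Score SD 3, gains of 2 and 3.5, drops of 2 and 1, long-term correlation 0.4, minimum 100 per cell (all Table 3); two-sided α = 0.05 (Sample size considerations).

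**Formulas.** SD of change = 3 × √(2 × (1 − 0.4)) = 3.286. Power = Φ(Δ/SE − 1.96). With n = 100 per cell:
- three-way contrast (HA1): SE = 3.286 × √(8/100) = 0.930
- two-way contrast at one level of the third factor (HA2): SE = 3.286 × √(4/100) = 0.657
- two-way contrast pooled over the third factor (HA2): SE = 3.286 × √(2/100) = 0.465
- mode pooled over all strata (HA3): SE = 3.286 × √(1/200) = 0.232

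**Step 1: reproduce the plan's figures with Δ = 2.5 throughout.** HA1: 2.5/0.930 = 2.69, power 0.77 (stated 0.80). HA2 at one level: 2.5/0.657 = 3.80, power 0.967 (stated 0.97). HA2 pooled would be above 0.999, so the stated 0.97 is the one-level contrast. HA3: above 0.99, as stated. The published powers therefore rest on 2.5 points.

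**Step 2: the effect on the analysed scale.** Brochure loses 2 and video loses 1, so the mode difference is 1.0 point over 12 months.

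**Step 3: power on the analysed scale, 100 per cell.** The plan gives no interaction size on this scale, so two assumptions are shown. Assumption A carries over the rule that interactions are similar to the mode effect (1.0 each). Assumption B borrows Aim 1's increments of 0.75 per interaction order: 1.0 + 0.75 = 1.75 for HA2 and 1.75 + 0.75 = 2.5 for HA1.

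| Hypothesis | Stated | A: 1.0 | B: 1.75 / 2.5 |
|---|---|---|---|
| HA1 | 0.80 | 0.19 (z = 1.08) | 0.77 (z = 2.69) |
| HA2, one level | 0.97 | 0.33 (z = 1.52) | 0.76 (z = 2.66) |
| HA2, pooled | not stated | 0.58 (z = 2.15) | 0.96 (z = 3.77) |
| HA3, mode pooled | 0.99 | 0.99 (z = 4.30) | 0.99 (mode effect still 1.0) |

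**Step 4: favourable variants under A.** With all 150 per cell and no attrition, HA1 is 0.26 and HA2 is 0.46 to 0.75. With a random-intercept slope over five time points and an arm main effect, at 100 per cell, HA1 is 0.22 and HA2 is 0.40 to 0.67. Reaching 0.80 for HA1 at 1.0 point would take about 679 per cell.

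**Step 5: the aligned alternative.** For the 12-month score adjusted for the pre-information score, the residual SD is 3 × √(1 − 0.4²) = 2.750. The three-way SE is 2.750 × √(8/100) = 0.778. A 2.5-point three-way contrast gives z = 3.21 and power 0.90.

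**The case against.** The strongest counter-argument is that the planned model need not estimate 1.0 point. The linear predictor displayed for Aim 2 has an intercept, time and time-by-mode, but no main effect of mode. Fitted by generalised least squares to Table 3's own means (post-information 3.5 and 2, falling linearly to 2.5 and 0; five time points; random intercept with correlation 0.4), that form gives a time-by-mode coefficient of about 1.95. If the interactions were also that size, power would be about 0.81 for HA1 and 0.98 for HA2 at one level, close to the stated values. This shows that the model is ambiguous, and it stands to that extent. The 1.95 arises only because the common intercept pushes the 1.5-point initial difference into the slope. The prose of the same section lists mode among the independent variables, and with mode included the slope difference is 1.0.

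It is also fair that decline from the level reached is a legitimate meaning of retention, and that a contrast against the pre-information score counts the short-term difference a second time. Both stand as reasons to choose deliberately. Neither justifies sizing on one scale and analysing on the other.

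A reader might infer more than the document supports:
- *That power for the interactions is simply 0.19 and 0.58.* Those figures need assumption A, which the plan does not state on the decline scale. The 0.58 is a pooled contrast and is not comparable with the stated 0.97; the like-for-like value is 0.33.
- *That the analysis will reverse the answer.* The example under the concern is hypothetical. On the plan's figures video gains more and loses less, so both scales favour video.
- *That return to the pre-information level is ignored.* The plan does intend to examine it. What it lacks is a stated between-arm test on that scale.
- *That 0.77 for HA1 at 2.5 points is a further error.* The correlation is given as a minimum, and 150 per cell less 25% leaves about 112, where power is 0.81.

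**Conclusion.** The point holds as an inconsistency in the current text: Table 3's effect size and Table 4's measurement use different reference scores, so the stated Aim 2 powers do not describe the analysed contrast. The mode effect on the analysed scale is 1.0 point, directly from Table 3's drops. HA3 pooled over strata keeps power of 0.99. For HA1 the power lies between about 0.19 and 0.77. For HA2 it lies between 0.33 and 0.76 at one level of the third factor, or between 0.58 and 0.96 pooled. The lower ends assume interactions of 1.0 point and the upper ends assume Aim 1's 0.75-point steps. All assume SD 3, correlation 0.4 and 100 per cell. The document does not settle which assumption applies, so the supportable conclusion is that the stated powers for HA1 and HA2 are not established for the planned analysis.

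**What to change.** Use one reference score for both the effect size and the analysis, and say which score baseline means each time it appears.

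**Preferred.** Define the Aim 2 between-arm contrast as the 12-month knowledge score adjusted for the pre-information score, with its interactions with language and health literacy. This matches the 2.5-point effect and the plan's own criterion that knowledge should exceed the pre-information level. HA1 power is about 0.90 at 100 per cell if the three-way contrast is 2.5. Report decline from the post-information score as secondary, and amend Table 4 to match. The cost is wording only, because pre-information scores are already collected. The downside is that 1.5 of the 2.5 points repeat the short-term difference tested in Aim 1, and the rate of forgetting becomes secondary.

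**Alternative.** Keep the post-information reference. Then restate the mode effect as 1.0, give explicit interaction sizes on that scale, restate the power with its range, and add the arm main effect to the displayed predictor. This also needs no new data, but it may mean acknowledging limited power for HA1 and HA2. With 1165 participants already past the three-month follow-up, the sample size is in effect fixed.
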